## Abstract

**Background:**

In Switzerland, there is a lack of adequate rehabilitation services, and effective coordination, that take into account the multifactorial health risks of older people. The literature shows that the hospitalisation rate in rehabilitation facilities has increased in recent years and that a gender bias exists. Additionally, there is little or no evidence available on the effect that a post-acute care programme might have over an extended period on functioning, quality of life and the informal network of older people. Therefore, the aim of this trial is to evaluate the sustainability of post-acute care within three nursing homes in Zurich, Canton of Zurich, Switzerland.

**Methods:**

The Prevention Admission into Nursing homes (PAN) study is a explorative, prospective, longitudinal pilot trial based on a convenience sample of three long-term care facilities in the Swiss Canton of Zurich. The proposed pilot study will examine the effects of a post-acute care programme on people aged ≥65 years with a post-acute care potential ≥ three admitted to any of the three post-acute care units (*n* = 260). Older people of all sexes admitted to one of the post-acute care units and likely to be discharged to home within 8 weeks will be eligible for participation in the study. The primary endpoint is functionality based on the Barthel Index. The secondary endpoints are independency based on delirium, cognition, mobility, falling concerns, frailty, weight/height/body mass index, post-acute care capability, quality of life, and lastly, the informal network. As part of process evaluation, a qualitative evaluation will be conducted based on constructive grounded theory to specifically analyse how the experience of informal caregivers (*n* = 30) can contribute to a successful daily life 6 months after discharge.

**Discussion:**

We expect to observe improved functional status and independence after the post-acute care programme. The qualitative evaluation conducted with caregivers will complement our description of the transition of older people towards living at home.

**Trial registration:**

This study is registered in the German Clinical Trials Register under DRKS00016647 (registered on 23.05.2019).

## Background

The World Health Organization recommends strengthening the availability of rehabilitation services in health systems [1]. It is generally accepted that rehabilitation should improve the functions and adaptability of those affected through the coordinated use of medical, social, occupational, technical and pedagogical interventions [2, 3].

Various terms for rehabilitation can be found in the literature: post-acute care (PAC), rehabilitative transitional care, geriatric rehabilitation, slow stream rehabilitation and acute transitional care. This study focuses on PAC. PAC takes into account that low-intensity therapies can be used to individually prepare older people for their return home, specifically those who are unable to return home immediately after hospital discharge [4]. Therefore, PAC can occur in many settings, such as inpatient rehabilitation facilities, long-term care facilities or home care [5]. Since the introduction of Diagnosis Related Groups, it has been observed that acute hospitals are increasingly referring older people who need follow-up treatment to rehabilitation facilities, in addition to homes and outpatient facilities [6]. Conducting a comprehensive geriatric assessment is standard practice in PAC facilities for determining a treatment plan, which increases the probability that people will not be institutionalised [7–9]. Those directly affected want their care to focus on a well-functioning social network and improve their mobility [10]. However, the extent to which PAC positively affects patient outcomes over an extended period has not been extensively investigated [8].

Although improved functional status does not guarantee a return home, it is a central outcome of rehabilitation and subsequent treatments [11]. A decline in functional capacity can lead to undesirable events, such as hospitalisation. Monitoring functional status can help detect changes in the health status of chronically ill people at an early stage [12], and the functional status of older people is an essential indicator for rehospitalisation [13–16]. It has also been shown that older people with reduced functional status and cognitive abilities often need long-term care [15, 17–19]. Hence, maintaining functional status is a central influencing factor of the ability to live independently at home or with the assistance of a home-care organisation [12, 16, 20, 21]. Functionality in rehabilitation care is predominantly measured using the Barthel Index (BI). However, although the BI is widely used in rehabilitation care, it is not described within the PAC context [22].

PAC is becoming increasingly important in international health care settings [23–25]. PAC and rehabilitation services for older people after hospital stays in Switzerland were therefore implemented in 2011 and are governed by cantonal policies [26]. Some cantons authorise nursing homes to deliver PAC, while other cantons opt for PAC delivery by hospitals or home-care providers [27]. The Canton of Zurich has opted to provide PAC in nursing homes and does so successfully [22]. However, equitable access and rehospitalisation issues remain [28]. Moreover, unlike in rehabilitation clinics and hospitals, quality improvement and control for PAC in nursing homes is not centralised [29].

The hospitalisation rate in rehabilitation facilities in Switzerland has increased in recent years and currently stands at 10.1 per 1000 inhabitants [30]. In 2017, the most frequent reasons for admission of older people to rehabilitation facilities were injuries, musculoskeletal diseases and cardiovascular diseases [31]. Older people referred to inpatient rehabilitation have more illnesses that require more intensive rehabilitation [32, 33], while the average length of stay has decreased in recent years [30]. Older people undergoing rehabilitation have a primary diagnosis linked with an average of six secondary diagnoses [31]. This indicates a high co-morbidity rate among older Swiss people in rehabilitation.

Furthermore, in Switzerland, there is a lack of adequate rehabilitation services, and effective coordination, that take into account the multifactorial health risks of older people [34, 35]. Problems associated with the discharge of older people from Swiss hospitals may be related to the study results of Koné and colleagues [34]. They found that discharge planning in Swiss hospitals is not standardised. Also, hospitals refer women less frequently to rehabilitation institutions than men [34]. It is unclear why women are less often rehabilitated than men of the same age with similar conditions.

In summary, based on this multifaceted background, there is a lack of evidence as to a) to what extent a PAC programme positively affects patient outcomes, specifically the functional status, and b) how sustainable these effects are over an extended period. This knowledge is pivotal in informing future care pathways for this co-morbid population and enhancing adequate rehabilitation services with an effective PAC programme.

### Aims and hypothesis

The aim of this study is to evaluate the sustainability of PAC using functionality as the primary endpoint, measured using the BI. We hypothesise that the PAC programme improves a patient’s functional status (measured using the BI) to a level that allows them to return home after completing PAC in the nursing home and maintain a moderate increase in BI for at least 6 months after discharge (odds ratio = 1.5). Based on the study’s exploratory nature, we assume that moderate improvements are associated with a substantial gain in independence.

## Methods

The SPICE framework is used to describe the study components [36]. The version adapted for this study contains the following elements: S = study design, setting, sample size, P = participants, I = intervention/issue of interest, E = Endpoints, including their specific analyses. Comparison (C) has been omitted, as this is not a clinical trial.

### Study design and setting

The Prevention Admission into Nursing homes (PAN) study is a three-site, multicentre, exploratory, prospective, longitudinal pilot study in Swiss nursing homes without a control group. All centres (*n* = 3) are located in Zurich and the study will examine older people (*n* = 260) enrolled in PAC treatment. Additionally, a qualitative process evaluation will assess relatives’ perspectives (*n* = 30).

This study will be led by Zurich University of Applied Science’s health department and the department of Nursing Homes of the City of Zurich (PZZ) and will last approximately 24 months.

### Sample size

The sample size calculation was based on the primary endpoint, the BI, for which we model the cumulative probability that the i-th BI Y_it_ will fall into the j-th category or below:

1$$logit\left(P\left({Y}_{it}\le j\right)\right)={\theta}_j-{\delta}_1\left(t{1}_{it}\right)-{\delta}_2\left(t{2}_{it}\right)-u\left({patient}_i\right)$$

i corresponds to the index for observations at time t, j represents the index for categories, {*θ*} is the cut-points, *δ*1 corresponds to the change in BI between PAC entry (baseline) and PAC exit, and δ2 is the change in BI between PAC entry and follow-up measurement at home after 6 months. Patient effects (random effects) are designed as independent and identically normally distributed:

2$$u\left({patient}_i\right)\sim N\left(0,{\sigma}_u^2\right)$$

Of vital importance for the evaluation of the sustainability of PAC is parameter δ2, for which the following hypothesis will be tested:

3$${H}_0:{\delta}_2\le \kern0.5em 0.4,\kern1.5em {H}_1:{\delta}_2>0.4$$

The expected improvement in BI under the alternative hypothesis is >0.4 logits, which corresponds to an odds ratio (OR) of about 1.5. The required sample size to detect an effect under the alternative hypothesis was determined by simulation. We assumed a significance level of α = 0.05 (two-sided test) and a target power of 0.8 (β = 0.2). The obtained power is based on 500 iterative analogue model estimates and was performed for different levels of patient-specific autocorrelation (intra-class correlation [ICC] = 0.1, 0.2, 0.4). As is usual with mixed-effects models, the sample size decreases with increasing ICC (see Fig. 1).

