Treatments with a rehabilitative approach are characterised by close interprofessional cooperation focusing on functional activities, education and psycho-social support [37]. Physicians are primarily responsible for PAC assessment, drug treatment, follow-up and evaluation. Therapeutic specialists, such as physiotherapists and occupational and speech therapists, are tasked with improving functioning, and nurses transfer and integrate (re)gained functions into the daily lives of older people. For example, the handgrip strength regained through targeted physiotherapy is transferred to everyday life through targeted nursing interventions. Patients are given sufficient time and individual support to select, prepare and eat their bread rolls for breakfast independently instead of simply feeding them. Overall, providing advice, particularly on mobility and self-care, to patients and their caregivers is an essential nursing intervention in PAC [37]. Social service providers carefully plan the return home and subsequent outpatient care. Furthermore, they initiate necessary measures in collaboration with the primary relatives.

A PAC programme lasts an average of 8 weeks and a maximum of 10 weeks based on the PAC potential assessment. If, after this time span, a return home is not possible, even with appropriate support, suitable alternatives are explored together with the affected person. In cases where a return home is likely after an extended stay, the older person is transferred to a specialised nursing ward to attain adequate independence and functioning.

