### Statistical analysis

Data analysis will be performed using R-Project software version 3.5.2. The socio-demographic data will be analysed descriptively (frequencies, central tendencies, standard deviations). For the primary endpoint, the BI, we will estimate unadjusted cumulative odds using the basic model presented in the sample size section to detect BI changes between baseline and follow-up measures. The model will further be adjusted for age, sex, and secondary endpoints mobility and frailty, which have been identified as driving factors leading to institutionalisation in a nursing home. Both unadjusted and adjusted OR with corresponding 95% confidence intervals will be reported. Similarly, unadjusted and adjusted generalised linear mixed-effects models of the appropriate family and link function will be used to estimate the parameters of the secondary endpoints. Statistical significance will be established at *p* < 0.05.

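### The primary model has only a patient intercept, so the standard error of δ2 assumes that all three visits are equally correlated; a patient-clustered variance would remove that dependence

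*Protocol article*

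**What the plan says.** In the Sample size section, equation 1 is a cumulative-logit model with cut-points, a shift δ1 (entry to exit), a shift δ2 (entry to 6 months after discharge) and one patient term. On that term the article says: "Patient effects (random effects) are designed as independent and identically normally distributed". The decisive parameter is named: "Of vital importance for the evaluation of the sustainability of PAC is parameter δ2". The hypotheses are H0: δ2 ≤ 0.4 and H1: δ2 > 0.4, with α = 0.05 described as two-sided.

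The Statistical analysis section makes this the primary analysis, fitted "using the basic model presented in the sample size section to detect BI changes between baseline and follow-up measures". Its adjusted version adds fixed covariates only: "The model will further be adjusted for age, sex, and secondary endpoints mobility and frailty". Odds ratios with 95% CIs are to be reported. The article mentions no patient-specific change, other correlation structure or robust variance.

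Power came from 500 simulated fits of an analogous model at ICCs of 0.1, 0.2 and 0.4. The plan uses 0.2 and says that no empirical ICC was available.

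On timing, the Intervention section says: "A PAC programme lasts an average of 8 weeks and a maximum of 10 weeks". T3 is 6 months after discharge, in the home.

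**The concern.** With a single patient intercept, the latent correlation is the same for T0–T1, T1–T3 and T0–T3, and on the logit scale everyone moves by the same amount. The schedule gives reason to doubt this. T0 and T1 lie about 8 weeks apart in the same nursing home. T0 and T3 lie about 8 months apart, across a move home. The Endpoints section also allows the Barthel Index to come from observation or from interviews with patients, relatives or staff, so the source may change after discharge.

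The cumulative-logit model fixes the residual scale, so its one intercept variance has to average the three correlations. The contrast that decides the study uses the pair most likely to fall below that average. In that case the p-value and CI for the primary odds ratio claim more precision than the data hold. The power simulation could not reveal this, because it used an analogue of the same model.

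**Working it through.** **The plan's own figure.** The article states 200 evaluable patients for 80% power at ICC 0.2. Simulating equations 1 and 2 with N = 200 and δ2 = 0.4 tested against 0 gave power of 0.61–0.65 two-sided and 0.74–0.77 one-sided (5, 10 or 21 equal-probability categories, assumed because the article gives none). Only a one-sided variant with 5 categories and the total variance fixed at π²/3 reached 0.80. The figure was not reproduced; that is a separate matter, and nothing below depends on it.

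**Closed form (linear analogue).** Let r01, r13 and r03 be the visit correlations and r̄ their mean. The true variance of the mean T0–T3 change is proportional to 2(1 − r03). A random-intercept model takes it as 2(1 − r̄). Hence

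- true SD / model SE = √[(1 − r03)/(1 − r̄)]
- two-sided size = 2[1 − Φ(1.96 / ratio)]

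Example, 0.8/0.6/0.48: r̄ = 1.88/3 = 0.627; ratio = √(0.52/0.373) = 1.18; size = 2[1 − Φ(1.66)] = 0.097.

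At r̄ = 0.2, the planned ICC: r03 = 0.1 gives √(0.9/0.8) = 1.061 and size 0.065; r03 = 0 gives √(1/0.8) = 1.118 and size 0.080, the maximum for non-negative r03.

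**Simulation.** The protocol's model was fitted by maximum likelihood to 700 data sets per pattern, with N = 200 complete, 10 categories and δ2 = 0. All correlations are assumed. The Monte Carlo error near 5% is √(0.05 × 0.95/700) ≈ 0.008.

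| T0–T1 / T1–T3 / T0–T3 | r̄ | Ratio | Closed-form size | Simulated, model SE | Simulated, clustered SE |
|---|---|---|---|---|---|
| 0.2/0.2/0.2 | 0.20 | 1.000 | 0.050 | 0.056 | 0.049 |
| 0.3/0.2/0.1 | 0.20 | 1.061 | 0.065 | 0.064 | 0.050 |
| 0.3/0.3/0 | 0.20 | 1.118 | 0.080 | 0.076 | 0.053 |
| 0.6/0.6/0.6 | 0.60 | 1.000 | 0.050 | 0.057 | 0.053 |
| 0.6/0.4/0.2 | 0.40 | 1.155 | 0.090 | 0.084 | 0.054 |
| 0.7/0.5/0.3 | 0.50 | 1.183 | 0.098 | 0.094 | 0.059 |
| 0.8/0.5/0.4 | 0.57 | 1.177 | 0.096 | 0.097 | 0.053 |
| 0.8/0.6/0.48 | 0.63 | 1.180 | 0.097 | 0.101 | 0.053 |
| 0.5/0.6/0.7 | 0.60 | 0.866 | 0.024 | not run | not run |

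The last row shows the reverse case: √(0.3/0.4) = 0.866, so the interval is too wide.

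A second set used 260 × 0.7 = 182 patients and δ2 = 0.4. Patterns 0.6/0.5/0.4, 0.7/0.6/0.4, 0.8/0.6/0.4 and 0.85/0.6/0.4 gave two-sided error of 6.3%, 8.0%, 9.1% and 10.5% (upper tail 3.3–5.0% against 2.5%). The clustered variance gave 3.9–5.0%.

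**Patients who change differently.** Here data were generated at ICC 0.2 with a random individual change, and size was measured around the model's own mean estimate.

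- Change at T3 only, linear in time, or shared by T1 and T3: SD 1 logit gives about 0.05; SD 2 gives 0.062–0.066; SD 3 gives 0.075–0.080.
- Independent changes at T1 and T3, SD 2: ratio 0.94, size 0.039.
- Extra variation at T1 only, SD 2: ratio 0.89, size 0.030.
- In the first group at SD 2–3, a true δ2 of 0.40 was estimated as 0.27–0.33. Rejection of 0.4 in the upper direction was only 0.013–0.025.

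**The case against.** A random-intercept cumulative-logit model is a conventional choice for three ordinal measurements. This is an exploratory, uncontrolled pilot, and robust variances or sensitivity models are often left to an analysis plan, which is not shown. That limits the weight of the point. It does not remove it, because the article writes the model out and names it as the primary analysis.

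A reader might infer more than the document supports:

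- **That the interval is too narrow whenever patients do not change alike.** It is too narrow only if the T0–T3 correlation is below the mean of the three. The reverse patterns above are conservative, and an SD of 1 logit in individual change makes almost no difference.
- **That the error rate doubles.** About 10% needs fairly high correlations that decay with time (means of roughly 0.5 to 0.6). The protocol explores ICCs only up to 0.4, where an assumed 0.6/0.4/0.2 gives about 8–9%. At 0.2 the ceiling is about 8%. With no empirical ICC, 0.2 does not bound the risk, but the document does not establish the higher values either.
- **That false claims of sustained gain become more likely.** The upper tail rises in the correlated-data patterns, but large heterogeneity in change also pulls δ2 towards zero. Rejection in the direction of H1: δ2 > 0.4 then need not rise and can fall.

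**Conclusion.** The point holds in a limited form. The stated primary model makes the standard error of δ2 depend on equal correlation among visits at about 0, 2 and 8 months, across a change of setting, and δ2 uses the most distant pair. If correlation falls with time, the standard error is understated, by a ratio of up to about 1.18 in the patterns tabulated. Two-sided size is then about 6–8% at a mean correlation of 0.2 and about 8–10% at higher, decaying correlations. If T1 is the odd visit, the error runs the other way.

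These figures rest on assumed correlations and category counts and on complete data. Simulation and closed form agree within Monte Carlo error. The adjusted model was not simulated. The direction of the error cannot be known in advance, and that favours a variance that does not depend on the pattern.

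**What to change.** Keep equation 1 for the point estimates. State that the tests and 95% CIs for δ1 and δ2, unadjusted and adjusted, use a patient-clustered robust (sandwich) variance or a bootstrap that resamples whole patients. Add a model with patient-specific random change as a sensitivity analysis: the clustered variance corrects the standard error but not the attenuation of δ2. Apply the same to quality of life, the only secondary endpoint measured at three visits. With two visits there is only one correlation, so the question does not arise.

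Cost: a sentence in the analysis section, a few lines of code and no new data. The CI for δ2 becomes up to about 20% wider if correlations decay and is essentially unchanged if they do not.

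### The primary null boundary (δ2 = 0.4) equals the hypothesised effect (OR about 1.5), so the stated 80% power at n = 200 is not tied to any coherent null and alternative

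*Protocol article*

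**What the plan says.** All places are in the protocol article.

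- **Sample size, parameter.** The test concerns δ2: "δ2 is the change in BI between PAC entry and follow-up measurement at home after 6 months".
- **Sample size, equation 3.** H0: δ2 ≤ 0.4 against H1: δ2 > 0.4, on the log-odds scale.
- **Sample size, effect.** "The expected improvement in BI under the alternative hypothesis is >0.4 logits, which corresponds to an odds ratio (OR) of about 1.5".
- **Sample size, error rates.** "We assumed a significance level of α = 0.05 (two-sided test) and a target power of 0.8 (β = 0.2"). Power was simulated with 500 model fits. With an ICC of 0.2 this gave 200 people, raised to 260 for dropout.
- **Aims and hypothesis.** Participants are expected to "maintain a moderate increase in BI for at least 6 months after discharge (odds ratio = 1.5").
- **Statistical analysis.** The model from the sample size section is to be used "to detect BI changes between baseline and follow-up measures", with unadjusted and adjusted odds ratios, 95% confidence intervals and significance at p < 0.05. No null value is stated there.

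**The concern.** A power statement needs a null value and a separate effect at which power is evaluated. Here only one number, 0.4 logits or OR 1.5, is offered for both. At the boundary of a null hypothesis, the rejection probability is the type I error, so 80% power cannot belong to the pair of values on the page.

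Two things are at stake. The first is the justification of n = 200, which cannot be traced to a stated test. The second is how the primary result will be read. Suppose the estimate is δ2 = 0.4 with a standard error of 0.178 (an assumption-based value, see the working). The 95% interval is 0.4 ± 1.96 × 0.178 = 0.051 to 0.749, or OR 1.05 to 2.11. Against a null of zero this is a positive result. Against equation 3 it is not. A reader cannot tell from the article which conclusion the investigators have committed to.

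**Working it through.** **Inputs from the article.** Null boundary 0.4; hypothesised OR 1.5; α = 0.05, called two-sided; power 0.80; n = 200 evaluable; ICC 0.2; measurements at entry, exit and 6 months.

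**Inputs assumed.** The article does not give the number of BI categories in the model, the cut-points or δ1. Equal-probability categories were assumed, with K from 3 to 21 (a 0–100 score in steps of 5 has 21 levels). Where the two changes had to be specified together, δ1 was set equal to δ2.

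**1. Same number.** exp(0.4) = 1.49 and ln 1.5 = 0.405.

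**2. Rejection probability as written.** Power = Φ((δ2 − 0.4)/SE − z).
- At δ2 = 0.4 the first term is zero. The result is Φ(−1.96) = 2.5% or Φ(−1.645) = 5%, for any n, ICC or K.
- At OR exactly 1.5 (δ2 = 0.405) and n = 200, it is 2.7% or 5.3%.

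Simulations of equation 1 at n = 200 and ICC 0.2 with true δ2 = 0.4:

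| Categories | Runs | z > 1.96 | z > 1.645 |
|---|---|---|---|
| 10 | 1000 | 2.4% | 4.9% |
| 5 | 500 | 1.4% | 3.0% |
| 10 | 300 | 3.7% | 5.0% |

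These scatter around 2.5% and 5%, as simulation error of about 1 percentage point would produce. At n = 260 (5 categories) the figures were 3.0% and 5.8%, so a larger sample does not help.

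**3. Attempt to reproduce 80% at n = 200.** The approximation is SE(δ2) = √(6 / (n(1 − 1/K²))).
- K = 5: √(6/(200 × 0.96)) = 0.177. K = 10: √(6/(200 × 0.99)) = 0.174. The 1000-run simulation gave 0.178.
- Null 0.4, true 0.4: about 2.5% or 5%, from step 2.
- Null 0, true 0.4, two-sided: K = 5 gives Φ(0.4/0.177 − 1.96) = 62%, and K = 10 gives 63%. K = 3 gives 59% and K = 21 gives 64%. Simulation gave 58% (5 categories) and 60% (10 categories). The range is about 58–64%.
- Null 0, true 0.4, one-sided 0.05: about 69–75%.

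Neither null reproduces 80% under these assumptions.

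**4. Effect needed if the null stays at 0.4.** δ2 = 0.4 + (1.96 + 0.84) × SE.
- K = 5: 0.4 + 2.80 × 0.177 = 0.90, OR 2.45. K = 10: 0.4 + 2.80 × 0.174 = 0.89, OR 2.43.
- Simulation at δ2 = 0.9 with the 1.96 cut-off gave 75% (5 categories) and 79% (10 categories).

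**5. Sample size if the null moves to zero.** With SE = 0.178 at n = 200, 80% two-sided power needs 200 × (2.80 × 0.178/0.4)² ≈ 311 evaluable. Across K = 3 to 21 the approximation gives 296 to 332.

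**The case against.** **The inequality sign.** Both H1 and the expected improvement are written as greater than 0.4, so a larger effect may have been intended. That is possible, but power must be evaluated at a particular value. The only one given is an OR of about 1.5, and the aims state it without the inequality.

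**A misprinted null.** A simulated 80% cannot come from testing 0.4 against 0.4, so the simulation used another null or another effect, most likely a null of zero. This is a strong point. A reader might infer from equation 3 that the trial really has 2.5–5% power, or will almost surely fail if its hypothesis is true. The article does not support that forecast. The low figure is what follows if the printed test is applied at the printed effect.

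**The statistical analysis section.** A reader might infer that this section contradicts equation 3 by testing against zero. It does not say so. It names no null and refers back to the model in the sample size section, and zero as the software default would be an assumption. The section also already commits to 95% confidence intervals. Comparing the lower limit with exp(0.4) = 1.49 would carry out equation 3 at the upper 2.5% level, which makes the sidedness mismatch minor. What remains is that the primary p-value has no stated reference value.

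**An exploratory, uncontrolled pilot.** This is true, and estimation with intervals is its natural output. The article nevertheless sets out a formal hypothesis, α and 80% power, and derives its sample size from them.

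**Conclusion.** The hypothesis and power statement are wrong as written. The null boundary is the only effect size named, and rejection there is about 2.5% (upper tail of two-sided 0.05) or 5% (one-sided 0.05). That result is exact and needs no assumption about n, ICC, categories or cut-points. The stated 80% at n = 200 therefore lacks a coherent null and alternative, and the one-sided hypotheses do not match the two-sided label.

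The remaining figures are softer. Power of roughly 58–64% against zero, and the need for δ2 of about 0.9 against 0.4, rest on assumed equal-probability categories; the simulations behind them also assume ICC 0.2. A reader might conclude that moving the null to zero is a mere correction of wording that restores 80%; under these assumptions it does not. Nor do the figures prove that n = 200 is too small, because the simulation settings are not in the article. A condensed article may leave those settings out, and their absence is not the fault here.

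The defect affects the sample-size justification and the reading of the primary result. The data to be collected and the model to be fitted are unaffected.

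**What to change.** Choose one null and use it in the aims, the sample size section and the statistical analysis section, with matching sidedness:

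- **(a)** Test H0: δ2 = 0, two-sided at 0.05, with 0.4 (OR about 1.5) as the planning alternative. Read the already planned 95% confidence interval against OR 1.5 descriptively.
- **(b)** If exceeding OR 1.5 is the success criterion, keep H0: δ2 ≤ 0.4, name the larger δ2 at which power is 80%, and state the one-sided α.

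In either case, rerun the simulation, restate the power at the planned n, and report the number of categories, the cut-points and δ1. In the statistical analysis section, state the null value to which the primary p-value refers.

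The cost is rewording in three places, one rerun of the simulation, and a stated power that may be less favourable than 80%. Nothing changes in data collection.
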